## Abstract

**Background:**

Interventions on adolescents’ lifestyle are important, but the main mechanisms that explain the changes (mediating variables) on lifestyle are unclear. This paper presents the rationale and methods of an intervention program focused on promoting active and healthy lifestyles (especially physical activity [PA] practice and reducing screen time) among Brazilian students-the *Fortaleça sua Saúde* program (Portuguese for “strengthen your health”).

**Methods/Design:**

This is a school-based cluster-randomized controlled trial. Three intervention and three control (no intervention) full-time public schools were randomly selected in Fortaleza, northeastern Brazil. Students (*n* = 1,272) from classes in Grades 7–9 were eligible, and 1,085 (548 in the intervention and 537 in control schools) completed the baseline and follow-up measures. The program duration was approximately four months and took place in 2014. Intervention strategies focused on teacher training, activities on health in the curriculum, active opportunities in the school environment (the availability of equipment for PA), and health education (health materials for students and parents). Data collection was undertaken before and immediately after the intervention. The primary variables included the practice of PA (weekly PA volume, PA behavior change stage and preference for PA during leisure-time) and screen time (TV and computer/video games). Potential intrapersonal, interpersonal and environmental mediators of PA and screen time were evaluated by a standardized questionnaire. Other lifestyle components (e.g., eating habits, substance use), psychological (e.g., self-rated health, body satisfaction) and biological (general and abdominal obesity) aspects, as well as academic performance were also evaluated in the total sample. Depressive symptoms, eating disorders, sleep quality, objectively-measured PA, and sedentary time were evaluated in obese students.

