## Methods

### Aim and study design

This study was descripted following the Consolidated Standards of Reporting Trials (CONSORT) recommendations (Additional file 1). This is a cluster-randomized controlled trial and the school was the sample selection unit [27]. The primary objective of the *Fortaleça sua Saúde* program was to determine whether a multicomponent program (teacher training and activities on how to discuss health topics in the general curriculum and PE classes, active opportunities in the school environment and health education in the school community) would increase PA practice and reduce screen time among full-time elementary students (Grades 7–9) in Fortaleza, northeastern Brazil. A further primary objective was to identify the effectiveness of the program on intrapersonal, interpersonal and environmental variables related to PA and screen time, and to determine which of these variables mediate active lifestyle changes. The program’s secondary objectives included: (i) to determine whether the program is also effective for different health factors (e.g., nutritional status, health behavior, quality of life, and others); (ii) to identify its effectiveness for addressing eating disorders, sleep quality and objectively-measured PA and sedentary time among obese students; and (iii) to evaluate the program execution, including indicators of the implementation, maintenance, and costs of this program.

The participation of the students involved in this study was authorized by the parent/guardian, by signing the informed consent form. The National Research Ethics System (protocol No. 17366313.9.0000.0121) approved this research project and it follows resolutions 196 and 251 of the National Health Council. Each school will receive a final report containing the program results and practical recommendations for application in schools.

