➢Pamphlets to students in the classroom or schoolyard: 1) PA and health; 2) screen time use and health; 3) eating behaviors	√ *Primary*: IP (knowledge, attitude, types and health recommendations)	√ School manager/Teachers
	√ *Secondary*: EP (social and family support) and ENV (opportunities in school and home)	
➢Pamphlets to parents in meetings or visits to schools: 1) PA and family; 2) screen time use and family	√ *Primary*: EP (social and family support, norms and modeling) and ENV (opportunities in school and home)	√ School manager/Teachers
	√ *Secondary*: IP (risks/benefits, types and health recommendations)	

*PA* Physical activity, *PE* Physical education

^a^Potential PA and reducing screen time mediators that are included in the Socioecological and Health Promotion School frameworks and were focused during these strategies: IP: intrapersonal mediators (e.g., knowledge, types of PA or screen time, risks and benefits, self-efficacy, perceived barriers); EP: interpersonal mediators (e.g., peers, teachers and parents modeling, support and norms); ENV: environmental mediators (e.g., family environment, school environment and environmental)

Other theoretical aspects were considered for measurement of the study variables. Socio-cognitive theory indicates that there are both intrinsic and extrinsic factors associated with individual behavior [30]. Transtheoretical theory emphasizes behavior during the stages of change [31], and socioecological theory [29], highlights the role of the environment on an individual’s behavior. Thus, these aspects were also considered in the planning of intervention strategies and definitions of the response-variables and mediating variables (see Tables 1 and 2).

**Table 2 Tab2:** Measured variables in the *Fortaleça sua Saúde* program

Dimension	Variables (reliability)^b^	
Primary Variables^a^		
PA	√ Weekly volume in moderate to vigorous PA and PA levels (ICC = 0.71)	
	√ PA-related behavior change (ICC = 0.76)	
	√ Preference for PA in leisure-time (ICC = 0.75)	
	√ Active commuting (walking/cycling) to school (ICC = 0.89)	
Potential PA mediators	√ *Intrapersonal:* Attitudes, self-efficacy and expectations (risks/benefits) (α range = 0.77–0.81)	
	√ *Interpersonal:* family, friend and teacher support (α range = 0.84–0.90)	
	√ *Environmental:* Neighborhood and school perception (α range = 0.61–0.78)	
Screen time	√ Daily time watching TV on weekdays and weekends days (ICC = 0.72 and 0.56)	

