### Statistical considerations

All sample size power calculations considered a statistical power of 80 % and a 5 % significance level for two-tailed tests. An odds ratio of two [35] was considered, that is, an odds ratio of two students from the intervention group becoming active after the program compared to their peers from the control group (www.openepi.com). Therefore, we estimated a sample of 480 subjects (1:1 between intervention and control groups). A cluster sample selection procedure can involve biases [35] and we, therefore, decided to duplicate the study sample for 960 schoolchildren. Additionally, considering a margin of 20 % for possible losses and refusals, ~1,200 students would be a sufficient sample size to detect a moderate-sized effect with 0.80 of power.

Moderate mediated effect sizes (structural equation models) of the intervention on the primary outcomes were expected (effect size of 0.30). We considered approximately 70 observed variables and the development of up to ten latent variables, considering the number of items included in the PA and screen time questionnaires. Thus, the recommended minimum sample size was 400 adolescents (www.danielsoper.com/statcal); a doubled sample due to the cluster sample selection procedure [35] and an anticipated 20 % dropout rate during the intervention estimating a sample of 960 students. Hence, ~1,200 students would be a sufficient sample size to detect a moderate-sized effect with 0.80 of power for the mediating variables.

We will test whether randomization resulted in a balanced distribution of variables between control vs. intervention students, as well as participating vs. dropout students. The variables that have differing distributions between the two groups will be entered as confounders in all models that test the effectiveness of the *Fortaleça sua Saúde* program.

The effect of the *Fortaleça sua Saúde* program on the primary variables will be tested in accordance with the intention-to-treat principle and in a completers-only framework using Mplus [55]. Intention-to-treat and completers-only analyses will be performed in order to identify the effect of the intervention condition in comparison to the control condition.

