Because the data have a multilevel structure (i.e., individuals are clustered within a school), the individual respondents may not necessarily be independent within each school. To correct this, the procedure for complex samples in Mplus will be used in relation to the school. Finally, the results will be reported in accordance with the Consolidated Standards of Reporting Trials (CONSORT) [56].

Statistical procedures proposed by MacKinnon and Dwyer [57] will be considered to identify the effectiveness of the program according to the primary variables and mediating variables, as a common method of intervention study on PA and screen time [13, 15]. Initially, changes in the primary variable (e.g., changes in weekly PA time) will be considered in a regression under the influence of the independent variable (intervention group). In the second model, the mediating variables will also be included in the regression model. Thus, the value of the mediated effect will be calculated by the difference coefficient of the independent variable between the two models [57]. The measure of effect will be expressed in standardized scores (beta) or as an odds ratio, depending on the nature and manner of treatment of the primary variables.

Regression models will also be built in order to identify the effectiveness of the program on secondary variables (e.g., body image, eating habits). The effectiveness of the program on variables among obese students will be analyzed separately using the same statistical procedures. The implementation and economic evaluation will be qualitatively and quantitatively analyzed, considering the different indicators of the evaluation of PA interventions [32]. All analyses will be built using the Mplus program and will be adjusted for possible confounding variables (behaviors at baseline and control variables). The level of significance for the study will be 5 % for two-tailed tests.

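### About ten behavioural variables are primary and unranked, each tested at 5 % in two unranked analyses, so the plan does not fix which result decides effectiveness

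*Protocol article*

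**What the plan says.** - **Abstract, Methods/Design.** The primary variables are said to include three for PA ("weekly PA volume, PA behavior change stage and preference for PA during leisure-time") and two for screen time (television; computer/video games).
- **Table 2, primary block.** Four PA rows: volume together with level, stage of change, leisure preference, and "Active commuting (walking/cycling) to school". Four screen-time rows: television time and computer/video-game time, each split into weekday and weekend, and a stage of change for each.
- **Methods, subsections on PA and screen time.** Travel mode to school and the two screen-time stages appear here too, so the body text agrees with Table 2.
- **Aim and study design.** The first primary objective joins more PA with less screen time. The mediators have their own: "A further primary objective was to identify the effectiveness of the program on intrapersonal, interpersonal and environmental variables".
- **Statistical considerations, analysis.** "Intention-to-treat and completers-only analyses will be performed in order to identify the effect of the intervention condition". Neither is called main or sensitivity. On the error rate: "The level of significance for the study will be 5 % for two-tailed tests".
- **Statistical considerations, sample size.** "All sample size power calculations considered a statistical power of 80 % and a 5 % significance level for two-tailed tests". The effect behind the first calculation is given next: "An odds ratio of two [35] was considered", for students becoming active, which is a binary outcome. The example given for the analysis is change in weekly PA time, which is continuous.

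**The concern.** A 5 % level limits the risk of a false claim to 5 % only when one test decides. Here several variables share primary status, each can be significant by itself, and each is analysed in two populations. The document names no lead variable, and it does not say whether success needs one result, one per domain, or all of them.

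As written, a significant result on travel mode or stage of change carries the same standing as one on weekly PA volume. If the two analysis sets disagree, nothing says which one counts. The Discussion part of the abstract links an effective program to public policy and to possible extension across the school system, so a chance finding on one of ten variables could carry real weight.

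**Working it through.** **Count of behavioural primaries**

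| Source | PA | Screen time | Total |
|---|---|---|---|
| Abstract | 3 | 2 | 5 |
| Table 2, by row | 4 | 4 | 8 |
| Table 2, weekday and weekend apart | 4 | 6 | 10 |
| The same, PA volume and level apart | 5 | 6 | 11 |

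Ten is used as the main count, because volume and level share one row and one reliability figure, whereas weekday and weekend times have separate ones.

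**Independent tests, one analysis set.** With m tests at 5 %, the chance of at least one false positive is 1 − 0.95^m.

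- m = 1: 5 %, the plan's stated level. The plan gives no family-wise rate to reproduce.
- m = 5: 1 − 0.7738 = 22.6 %
- m = 8: 1 − 0.6634 = 33.7 %
- m = 10: 1 − 0.5987 = 40.1 %
- m = 11: 1 − 0.5688 = 43.1 %

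**Correlated tests.** The variables are related, and the documents give no correlations, so a range was assumed. The test statistics were simulated as Z_j = √ρ·f + √(1−ρ)·e_j with standard normal f and e_j (100,000 draws), counting draws in which any |Z_j| exceeds 1.96.

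**Second analysis set.** The correlation between the two analyses of one variable is not given. It was approximated by the square root of the ratio of sample sizes: √(1,085/1,272) = 0.92, from completers and eligible students. For a single variable this moves the rate from 5 % to 6.8 %. With the 1,182 baseline students as denominator, √(1,085/1,182) = 0.96 and the rate is 6.4 %.

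| Assumed correlation between variables | 5 tests, one set / both sets | 10 tests, one set / both sets |
|---|---|---|
| 0 | 23 % / 30 % | 40 % / 51 % |
| 0.5 | 18 % / 24 % | 29 % / 37 % |
| 0.7 | 15 % / 20 % | 21 % / 27 % |
| 0.9 | 10 % / 13 % | 13 % / 17 % |

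Both-sets figures use the 0.92 correlation. All figures assume that each single test keeps its nominal 5 % level.

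**The case against.** **The decision rule is not stated.** These rates apply if any one significant primary counts as success, and the protocol never says that it does. Its objective joins PA and screen time with an and. This stands as a condition on the figures. It does not remove the problem. Suppose success required one significant variable in each domain, with independent tests. If neither domain truly changed, the chance of a false claim would be (1 − 0.95^4) × (1 − 0.95^6) = 0.185 × 0.265 = 4.9 %. If one domain truly changed and was detected, the chance of a false claim in the other would be 19 % (PA) or 26 % (screen time). Requiring all ten would remove the inflation, but the text does not require it.

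**An analysis plan may exist.** Multiplicity handling is commonly left to it, so its absence here is no fault. The point rests on what the article itself fixes: many unranked primaries, one level, two unranked analyses.

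**Stronger readings that a reader might infer.**

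- *Up to 28 primaries and a 76 % error rate.* Adding 8 PA and 9 screen-time mediator scales to 11 gives 28, and 1 − 0.95^28 = 76 %. Table 2 does place the mediators in the primary block. But the abstract and Statistical considerations name them apart from the primary variables, and a significant mediator would not show that PA rose or screen time fell.
- *The abstract contradicts Table 2.* Its wording is not exhaustive, and the Methods agree with the table. It is an abridgement to be aligned.
- *The sample size uses an outcome in neither list.* Becoming active is plausibly the PA level in Table 2's first row. What remains open is whether level or volume leads.
- *Registration in May 2015, after data collection in November and December 2014, fixes nothing.* Only the date is shown. The content is unseen, and the analyses are described as still to come.

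**Conclusion.** The concern holds for the behavioural primaries. The document gives primary status to about ten variables, names five in the abstract, ranks none, tests them at one 5 % level and does so in two analyses without an order.

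If one significant primary is enough, the false-claim risk in a single analysis set is 23 % for five and 40 % for ten independent tests, and 10 % and 13 % at a correlation of 0.9. The size depends on the unknown correlation and on that decision rule, but the rate is above 5 % throughout the range examined. The second analysis set adds less than a doubling, because the two sets share most students. Its greater harm is the freedom to choose when they disagree.

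The documents do not support extending this to the mediators as if they were further tests of the behavioural objective.

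**What to change.** Before analysis:

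1. Name one lead PA outcome: for example weekly moderate-to-vigorous PA volume adjusted for baseline, or the active/inactive PA level behind the sample size. Choose one, not both.
2. Name one lead screen-time outcome, with its definition.
3. Test the two with Holm at 5 % overall: the smaller p-value against 0.025 and, if that succeeds, the larger against 0.05.
4. Report the other behavioural variables as secondary.
5. Make intention-to-treat the main analysis and completers-only a sensitivity analysis.
6. Align the abstract with Table 2.
7. Keep the mediators as their own declared objective, which has its own sample-size calculation. Report them as a separate family, not as evidence that the behavioural objective was met.

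**Cost.** The change is mainly one of wording, with some loss of power. A test with 80 % power at 5 % two-sided has an expected statistic of 1.96 + 0.84 = 2.80. At 2.5 % the critical value is 2.24, and power is Φ(2.80 − 2.24) = Φ(0.56), about 71 %. That is the lower limit for either outcome under Holm. If the other outcome is significant at 0.025, the full 5 % level applies. The remaining behavioural variables lose primary status.

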**Discussion:**

If effective, this program will contribute to the development of public policies for the promotion of active and healthy lifestyles in youth, especially those from low- and middle-income countries. The main intrapersonal, interpersonal and/or environmental mediators of PA and screen time may also be indicated. Finally, we anticipate that the proposed strategies may be adaptable to public schools and may even be extended to the entire school system.

**Trial registration:**

ClinicalTrials.Gov: NCT02439827. Registration date: May 3, 2015.

**Electronic supplementary material:**

The online version of this article (doi:10.1186/s12889-015-2543-2) contains supplementary material, which is available to authorized users.

## Background

An active (i.e., regular physical activity [PA] as well as low levels of sedentary time) and healthy (i.e., attitudes positively associated with health, such as healthy eating habits) lifestyle can lead to many individual and collective benefits at any age [1–4]. However, a focus on the early years has been employed due to the potential present and future health impact on the population [1–5].

Although the benefits of active and healthy lifestyles are widely reported, few young people lead an active lifestyle. International data estimates that only two out of ten adolescents meet the PA recommendations (300 min or more of moderate to vigorous PA per week) [6]. In Brazil, the proportion of students who met this recommendation fell from 43.1 % in 2009 to 30.1 % in 2012 [7]. Additionally, other unhealthy lifestyle factors are common among young people (e.g., excessive screen time and inadequate eating) [6–8]. Thus, interventions focused on promoting active and healthy lifestyles in young people are a public health priority [3, 4, 9, 10].

Systematic reviews have summarized the evidence of interventions that aimed to promote PA [10–15] and reduce sedentary behavior [5, 10, 11, 15, 16] among young people. Important implications can be identified from these reviews. First, in general, interventions had modest effect on behavior change [10, 11, 14, 16]. Second, multicomponent programs (i.e., strategies focused on different settings and individuals from the school, the family and/or the community) had more promising results on the promotion of active lifestyles [5, 10–12]. Third, the school seems to be an appropriate setting for many of the intervention strategies [10–12, 15]. Finally, the effectiveness of programs on PA and on sedentary behavior-related variables (e.g., risks and benefits, self-efficacy, social support, environmental perceptions), and how these variables (i.e., mediating variables) explain active lifestyle changes among adolescents has been little explored [13, 15].

Specifically, systematic reviews have highlighted that interventions focused on mediating variables and how they work are still scarce [5, 13, 15, 16]. For example, Van Stralen et al. [15] found 18 interventions on mediators of PA, but most of the potential intrapersonal (e.g., knowledge, self-efficacy), interpersonal (e.g., social support, peer and family model) and environmental (e.g., perception and environmental characteristics) mediators associated with PA remained largely unexplored. Evidence on the mediators of reducing sedentary behavior among young people is even more limited [5, 15, 16].

An intervention program that sought to fill the gaps was the Transform-Us! program [17]. This intervention was carried out in 2011 and 2012 for a period of 18 months and involved almost six hundred 8 to 9 year-old children from Melbourne, Australia. The intervention activities were multicomponent, including changes in physical education (PE) classes, reducing uninterrupted sedentary time and promoting health education in school. Intrapersonal, interpersonal and environmental factors related to PA and screen time were measured [17].

Results from the Transform-Us! program [18] revealed important evidence of the role played by the perceived school environment and perceived social support from teachers as mediators of PA changes among children over time. However, it is questionable whether such results would similarly occur among adolescents given the fact that they have physical, psychological and social peculiarities [19]. Additionally, the Transform-Us! program and most of the evidence from systematic reviews [5, 11, 13, 15, 16, 20] are of high-income countries. Sociocultural and structural distinctions between countries allow exploration of whether the effectiveness of interventions promoting active lifestyle and their mediators occur similarly among low-and middle-income youth populations, such as in Brazil. Considering that most of the world’s population lives in these types of countries (see the World Bank’s population estimates at www.worldbank.org/depweb), interventions in these contexts are essential in order to know what adjustments and variables are necessary for an effective promotion of active and healthy lifestyles among young people in these sociocultural situations.

Based on these assumptions, this paper presents the rationale and methods of a cluster-randomized controlled trial aiming to promote active and healthy lifestyles among Brazilian students. This program was entitled *Fortaleça sua Saúde* (Portuguese for “strengthen your health”) and included students from elementary full-time public schools (Grades 7–9) from a municipality in northeastern Brazil.

